### Other relevant research

Complementary qualitative research will be conducted in three areas: tracking expenditure survey; parental perceptions of schooling; and assessment of programme characteristics that cannot be observed through standard surveys.

#### Public expenditure tracking

As the national programme is relatively new and in the process of scaling-up, there might be inefficiencies or leakages in the flow of funds running from the Ministry of Finance down to the school management committees. We suggest conducting research following the flow of funding from its initial allocation at the central level, to the regional offices, the mayors, the CGSs and the traders or small farmers involved. The research will allow a careful examination of all the stages of the financial transactions involved, highlighting the characteristics of the procurement system and identifying entry points for improved efficiency.

#### Focus groups with farmers, parents, children, teachers and local authority stakeholders

These focus groups are designed to obtain insights on the challenges and opportunities in terms of engaging small holder farmers in the food procurement process, determinants of parents’ and children’s decisions to attend school, as well as related issues linked to hunger and seasonality. Teacher attitudes and motivation will also be assessed. The focus groups will be conducted in a small sub-sample of communes/schools at baseline, at mid-term and during the follow-up survey.

#### Programme monitoring and process analysis

Survey data collection will be integrated in the regular project monitoring activities also supported by PCD that include school level monthly and quarterly data collection. Periodic visits (in some cases unannounced) will also be made to the project communities in order to observe nutritional characteristics of the meal served in school; pupils’ behaviour in class after the meals; modalities of cooking and storage; other aspects of project implementation that cannot be observed though a quantitative survey.

## Methods of analysis

The analysis will follow the intention to treat approach as protocol and as treated, using econometric and simulation analysis, for all the relevant outcomes of the intervention. Impact will be assessed for the different treatment arms using regression analysis to account for potential confounding variables, using a “difference-in-difference” estimator.

As enrolment rates in Mali are very low in rural areas (around 30%), one problem in conducting this analysis is that school feeding may bring to school children of very poor backgrounds with poor nutritional status and cognitive abilities to start with. This problem can be overcome econometrically by controlling for such confounders during the data analysis.

A further difficulty of difference-in-difference analysis is serial correlation [28] resulting from unobserved factors affecting the outcomes that are themselves correlated over time and that produce auto-correlated errors and invalid standard errors. Serial correlation affects estimated standard errors and can lead to erroneous acceptance or rejection of null hypotheses but not the estimation of the effect size of the intervention. Thus, it may lead to erroneously finding or not finding a statistically significant impact of the intervention. See [29] for an illustration of how this problem can be addressed by calculating clustered standard errors, a procedure that is easily implemented using the Stata software. Clustered standard errors will also be employed in all cases in which correlated outcomes are observed within the same unit of analysis, for example, when the impact of the intervention is analysed at the school level and test scores within the school are obviously correlated. Similarly, clustered standard error will be used at the household level when the project is affecting more than one child within the same family as in the case of the impact on siblings that was discussed in Section Impact on nutrition.

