### The national school feeding programme in Mali

In line with the National Decentralisation Policy and the 2009 National School Feeding Policy, programme implementation is decentralised to the community level, involving the communes and School Management Committees (CGS). The central government allocated nearly 5 million USD (2.6 billion CFA) in 2010 and 5.8 million USD in 2011 (3.1 billion CFA) from the national budget for food, cooking equipment and infrastructure rehabilitation and construction [8]. Funds are channelled directly through the Ministry of Finance to its Regional Offices which in turn send funds to the communes. Food commodities are procured from local markets by the communes or by the CGS. To date, there is no fixed food basket nor fixed ration specification. The budget allocated for food procurement is based on student enrolment figures obtained by the Ministry of Education and price estimates for staples at the beginning of the school year. The budget covers staples, including cereals and pulses and oil. Fresh vegetables to complement the school feeding ration are contributed by parents and the community through cash or in-kind contributions. Cooks are generally organised on a voluntary basis (also considered as the contribution to the program from the community) through the CGS.

Food provision consists of a school lunch meal served at noon (school is from 8 am to 12 am and then again from 3 pm to 5 pm). The food mainly consists of staples (rice, millet or sorghum) enriched with condiments, vegetables, vitamins and minerals depending on the source of provision. Figure 1 captures the key activities in the food procurement process currently in use in the national programme. Enrolment figures are collected by the Centres d’ Animation Pedagogicue (CAP), the equivalent of district education offices, through the CGS and passed on to the mayors to estimate the food requirements for school feeding. Mayors receive budgets from the Ministry of Finance on the basis of the enrolment/food requirements, then issue tenders, on the basis of a credit advance, to certified service providers (traders) to procure the food. The service providers (traders) then purchase the food from the market or from small-holders, and deliver it to the relevant schools.

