**Figure 1 F1:**
[figure not shown]
Stylised food procurement process in the national programme.

Mayors are public officials representing the democratically elected local authority within each commune. The office of the Mayor is responsible for the food procurement in all the relevant schools in the commune.

The purchase of food by mayors presents a number of problems [9]:

•Food is mostly purchased from traders rather than from small-holder farmers

•Food purchased by mayors is often unrelated to food habits of the beneficiary communities; it does not follow any specific nutritional advice, and its quality is uncertain

•Food is delivered to communities with delays and CGS are uncertain about deliveries

•Food can be easily in excess or deficit of needs because it is purchased based on rough estimates of enrolment (with low enrolment rates the margin of error can be large and the programme has the effect of increasing enrolment which is not accounted for in the allocation)^4^

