**Figure 3 F3:**
[figure not shown]
Overall programme theory of school feeding interventions.

It must be emphasised that the ability of the school feeding intervention to deliver the effects depicted in Figure 3 critically depends on the appropriate implementation of the programme. The management and implementation of the intervention involves several actors and scoping visits. A preliminary study undertaken by PCD [9] has shown that in Mali there are several problems of communication, supervision and monitoring among these different stakeholders. Programme success will also depend on the ability of communities to actively engage in the programme and in the strengthening of the public institutions involved. The issues of social accountability, ‘good governance’ and the links between accountability and programme effectiveness are important areas that this impact evaluation will explore in more detail.

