### Role of social accountability

The effectiveness of the programme could be considerably improved by improving the communication mechanisms between the actors involved, by strengthening the monitoring system, and by introducing elements of social accountability. On the institutional side, the introduction of a monitoring system and the creation of communication mechanisms between the different actors would likely have the effect of improving the programme performance (see Figure 12). Similar effects could be expected from a stronger engagement of the CGSs. The delegation of certain responsibilities to the CGSs could increase motivation and awareness of the programme among beneficiaries while at the same time ensuring a better implementation of activities, (such as monitoring of public officers’ performance and food procurement from small holders in the community). These effects would have a positive impact on all the intermediate and final outcomes of the intervention.

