### Threats to validity

The main potential threats to the internal validity of the study, including contamination, spill-over effects and Hawthorne-like effects were examined for each of the outcome indicators of Section Programme theory of the intervention. From Table 4 it seems that most threats could be avoided by:

i. assigning treatments to communes rather than to villages within communes in order to avoid contamination effects;

ii. avoid informing teachers and households of the control villages that the programme will be implemented after two years in order to avoid expectancy effects;

iii. adopting strategies in conducting cognitive and achievement tests that prevent teachers and children from over-performing.

**Table 4 T4:** Threats to internal validity

**Indicator**	**Metric**	**Spill-over and contamination**	**Hawthorne and placebo effects**
Schooling	Enrolment, attendance, drop-out and completion	Children may attend school from neighbouring communities to have access to meals	Expectation of coming programme in control villages
Cognitive ability	Raven’s matrices or other test	Very unlikely	Teachers’ and children’s attempts to over-perform in both project and control villages
Attention	Digit span or other test	Very unlikely	Teachers’ and children’s attempts to over-perform in both project and control villages
Learning achievement	Scores on language and math tests	Very unlikely	Teachers’ and children’s attempts to over-perform in both project and control villages
Physical growth	Anthropometric measures of height and weight	Children from other villages may access school meals	Very unlikely
PAL	Parents perceptions	Very unlikely	Very unlikely
Diet diversity	Household consumption	Very unlikely	Very unlikely
Micronutrient intake	Iron status, anaemia	Children from other villages may access school meals	Very unlikely
Income	Farm profits	Unlikely, if food purchases are made in control villages	Very unlikely
Social accountability	Parental monitoring and motivation	None at household level, possible at local Government level	Possible

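### Intention-to-treat, per-protocol and as-treated analyses are named side by side for all outcomes with none made primary, although the last two condition on what happens after randomisation

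*Protocol article*

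**What the plan says.** **Analyses.** The Methods of analysis section opens: "The analysis will follow the intention to treat approach as protocol and as treated", and continues "using econometric and simulation analysis, for all the relevant outcomes of the intervention". The next sentence plans to assess impact "using regression analysis to account for potential confounding variables, using a “difference-in-difference” estimator". No sentence ranks the three approaches. The section Trial oversight says that an independent expert group will approve the final analysis plan at the end of the study.

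**What delivery depends on.**
- Programme theory of the intervention, below Figure 3: "Programme success will also depend on the ability of communities to actively engage in the programme".
- Role of social accountability: giving the school management committees (CGS) more responsibility could "increase motivation and awareness of the programme among beneficiaries while at the same time ensuring a better implementation of activities".
- The national school feeding programme in Mali: "Fresh vegetables to complement the school feeding ration are contributed by parents and the community through cash or in-kind contributions".
- The same section, below Figure 1: "The office of the Mayor is responsible for the food procurement in all the relevant schools in the commune". Food is mostly bought through traders.

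**Design.** Random assignment and manipulation of treatments describes two schools in each of 58 communes, one allocated to feeding and one to control. HGSF+ or regular feeding is then allocated by commune.

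**The concern.** Intention to treat keeps the groups that randomisation formed. Per-protocol and as-treated analyses regroup or drop units by what happened afterwards: whether the programme ran in a school, or whether a child took it up. If the causes of delivery also affect schooling, learning or income, the regrouped comparison mixes the programme's effect with those causes.

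The protocol expects uneven delivery. It reports delays, uncertain deliveries and quantities that do not match need, and its Risks section mentions disruption of the service. The three analyses may therefore disagree. As written, nothing says which result is the trial's answer on the primary outcomes.

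**Working it through.** The documents give no figure for this bias, so there is none to reproduce. The check is a comparison of the texts, followed by a conditional calculation.

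**1. Order of the analyses.** Methods of analysis gives three approaches, one scope (all relevant outcomes) and no rank. Trial oversight places approval of the final plan at study completion. Nothing shown fixes the order earlier.

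**2. What the last two condition on.** The sets are undefined. They could be built on delivery at the school or on uptake by the child. Either is measured after randomisation. Delivery is tied partly to the community (engagement, CGS, parental contributions) and partly to actors above the village (mayors, traders).

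**3. What the planned estimator removes.** Suppose that, without the programme, delivering villages would exceed non-delivering ones by D0 at baseline and D1 at follow-up. Difference-in-difference compares changes, so only D = D1 − D0 can bias it. If the gap is constant, D = 0 and there is no bias. Regression removes only the part of D explained by measured covariates. What is left is selection on trends.

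**4. Conditional size.** Let a share f of the 58 feeding villages not deliver, and let D be the remaining trend difference in SD units. Neither is given in the documents; both are assumed. With the feeding villages' mean set to zero, deliverers average +fD and non-deliverers −(1−f)D.

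- As treated, commune pairing ignored, non-deliverers pooled with the 58 controls: bias = fD + f(1−f)D/(1+f) = 2fD/(1+f).
- Deliverers against controls, which is also the paired comparison when D is purely between villages: bias = fD.
- Paired comparison when D is purely between communes: bias = 0, because a commune whose feeding school does not deliver has two untreated schools and offers no contrast.

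| f | D | As treated, unpaired | Paired, village-level D | Paired, commune-level D |
|---|---|---|---|---|
| 0.1 | 0.2 | 0.04/1.1 = 0.04 | 0.02 | 0 |
| 0.2 | 0.3 | 0.12/1.2 = 0.10 | 0.06 | 0 |
| 0.3 | 0.5 | 0.30/1.3 = 0.23 | 0.15 | 0 |

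Appendix 1 gives a detectable difference in test scores of 0.23 SD for feeding versus control (rounded to 0.2 in its conclusions). The table shows what would follow from each pair of assumptions. It does not estimate the bias.

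**5. Direction.** Each expression is linear in D, so its sign follows D. If engaged communities improve faster, D is positive. But the list of procurement problems says that food can fall short because the programme raises enrolment and the allocation ignores this. Shortfalls may then occur where enrolment gains are largest, and the bias on enrolment would run against the programme.

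**6. HGSF+ versus regular feeding.** This comparison is between communes, so commune-level causes of delivery do not cancel. HGSF+ is also meant to work by improving delivery. Restricting to places that deliver well conditions on that mechanism and could hide its effect.

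**7. Error rates, illustration only.** A simulation used 58 versus 58 villages, 25 children each, intra-cluster correlation 0.15 (both from Appendix 1), zero true effect and 10% to 40% non-delivery. It modelled neither pairing nor difference-in-difference.
- Intention to treat rejected in about 5% of runs throughout.
- With correlation 0.3 between engagement and the village outcome, as-treated bias was 0.04 to 0.11 SD, with false-positive rates of 0.08 to 0.23. Per-protocol bias was 0.02 to 0.07 SD, with rates of 0.06 to 0.12.
- With no selection, the chance that at least one of the three tests was significant was still 0.06 to 0.09. The limit for three independent tests is 1 − 0.95³ = 0.143.

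**The case against.** Intention to treat is named first and is the only one called an approach, so the sentence may mean intention to treat supplemented by two further analyses. Reporting such analyses beside it is common. Defining analysis sets is normally left to the analysis plan, this is a condensed article, and an independent group will approve that plan. Much of this stands: the missing definitions are not a fault in themselves. What remains is that the article commits to all three for every relevant outcome, and nothing shown says which one supports the conclusions.

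A reader might be tempted to infer more than the documents support:
- **That villages will be sorted by delivery quality.** The sets are undefined; sorting by child uptake is equally possible.
- **That the bias favours the programme.** The allocation problem described above can push the other way.
- **That the bias is close to the detectable difference.** This treats D as a level gap, which difference-in-difference removes, and it ignores the pairing of schools within communes.
- **That the analysis will be chosen after seeing results.** The article gives the date of final approval. It does not say that no earlier plan exists.
- **That Table 4 supports the point.** The entry "Children from other villages may access school meals" concerns spill-over, which affects intention to treat as well and says nothing about communities determining delivery.

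**Conclusion.** The point holds in a limited form. The article lists three analyses with no primary one, and two of them condition on events after randomisation that the protocol itself links partly to community engagement. The planned adjustment does not remove selection on trends, so those two estimates can be biased either way.

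The size is unknown. Under the assumed pairs of f and D, with D as a trend difference, it ranges from zero (paired, commune-level cause) to 0.23 SD (unpaired, f = 0.3, D = 0.5). The simulated error rates also ignore pairing and difference-in-difference, so they are at most an upper illustration. The conclusion rests on reading *as protocol* as per protocol. It matters because the remedy is cheap and is worth most if made before outcome data are analysed.

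**What to change.** State now that intention to treat alone supports the conclusions: by randomised school within commune for feeding versus control, and by randomised commune for HGSF+ versus regular feeding.

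For feeding versus control, replace the naive per-protocol and as-treated estimates with a secondary complier effect, using random assignment as the instrument for the programme operating in the school. State the exclusion assumption, that assignment acts only through the programme operating. It needs defending here: the Risks section notes that a child may be worse off when parents believe that meals are served and they are not.

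For HGSF+ versus regular feeding, report intention to treat only, or label any delivery-based analysis as descriptive. The treatment there is training and accountability, so meals delivered is not a valid exposure.

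The cost is a few sentences. The data, the sample size and the software (Stata) stay the same. The downside is a wider interval for the complier effect. With no feeding in control schools and the delivery share taken as known, it is about 1/(1−f) times the intention-to-treat interval: 1.11, 1.25 and 1.43 times for f = 0.1, 0.2 and 0.3.

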### Main hypotheses and outcome indicators

We summarise here the expected impact of the intervention on education, nutrition and social protection discussed in Section Programme theory of the intervention.

•The intervention will have an impact on a small number of farmers in the intervention villages. Other persons in the village may benefit either directly or indirectly via an increase in income.

•The intervention will have a positive impact on enrolment, attendance and drop-out rates.

•The intervention will have an impact on cognitive abilities and class behaviour, including attention.

•The impact on learning (test scores) will be moderate as school quality is unlikely to change in the short term.

•The intervention will have a limited impact on physical growth of children because of the increase in PAL, substitution effects and the age range (6 to 17 years) of the targeted population. An impact on siblings of school-going children is possible if substitution effects are strong.

•The intervention will have a moderate impact on the diet because food purchases by communities and mayors do not follow nutritional guidelines and nutrition education is absent.

•The intervention will have little or no impact on micronutrient status as the food provision is not fortified and only moderate effects on diet diversity are expected.

•The overall impact of the programme will increase through the introduction of social accountability mechanisms and the strengthening of the monitoring and communication system.

Table 2 includes a list of the main outcome indicators of the study. Section Methods of analysis will describe how data will be collected using different survey instruments. All outcomes, including school attendance and test scores, will be obtained at the household level.

**Table 2 T2:** Main outcome indicators of the intervention

** Indicator**	** Metric**
Income	Farm profits
Distributional effects	Small farmers participating in the programme
Schooling	Enrolment, attendance, and completion
Attention	Digit span or other test
Learning achievements	Scores on language and math tests
Physical growth	Anthropometric measures of height and weight
Diet diversity	Household consumption
Social accountability	Parental monitoring and motivation

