Power calculations (see Appendix 1 for more details) and resource availability suggested the adoption of a sample of 25 households from the village areas of the 58 schools receiving the intervention and of 20 households in the village areas of the 58 control schools. Farmers will be oversampled in both areas in the following way: 10 out of the 25 households in the 58 intervention villages will be farmer households and 5 out of the 20 households in the 58 control villages will be farmer households. This distribution of the sample between farmers and non-farmer households and between project control groups allows the construction of comparable samples (see Table 3).

**Table 3 T3:** Summary of sample sizes

	**Communes**	**Schools**	**Households**	**Farmers**	**Children**^**1**^
Control	58	58	870	290	2,700
HGSF	29	29	435	290	1,500
HGSF+	29	29	435	290	1,500
TOTAL	58	116	1,740	870	5,700

Note: 1) the number of children in an estimate based on an average of 2 children per family in families with children and 1.5 children per family in farmer households.

Households were randomly selected in the catchment areas of the selected schools for the survey interviews.^6^ The definition of ‘household’ in Mali is not straightforward as many families share the same living compound and polygamous families are common. A recent study [27] found that adding descriptions to a “restricted” definition of household (a group of people who normally live in your household – adopted by the DHS) increases the number of adult male members reported during the interview. This, however, does have a very limited impact on household characteristics, such as per capita food consumption, assets and agricultural production. We recommend the use of the restricted definition adopted by the Rapid Household Survey 2006, which reflects the LSMS experience in collecting data in developing countries. According to this definition, a (restricted) household is a group of people who normally live and eat together. Members spending less than three months with the household within a year should be excluded. Families living in the same compound should be considered as different (restricted) households, though the consumption section of the questionnaire was carefully designed in order to take into account the common use of food resources. Polygamous households were treated as distinct households if wives live and cook in separate houses.

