In practice, the sampling of households was not conducted via a previous census as this was considered too costly in terms of time and resources. We opted for interviewing village chiefs and building a list of enlarged households in the villages covered by the sample school. The listing also included an approximation of the size of the enlarged households. In addition, a number of farmer households was oversampled in each village. Chiefs (and members of the CGSs) were asked to list which farmers they would contact if they were to purchase food within the village for the provision of school meals. This latter information was used to single out the surplus farmers in the area (up to 10 in the project villages and up to 5 in the control villages that will be interviewed).

Enlarged households were randomly selected (with inclusion probability proportional to size) from the list provided by the village chiefs, and listings of the restricted households within each selected enlarged households will then be developed through interviews with household heads. A restricted household with children aged 5 to 15 was then randomly selected within each selected enlarged non-farmer household, and we estimate that each household will have at least two children in this age group. A similar selection procedure was used for farmer households when these exceed the numbers of 10 and 5 in the project and control villages, respectively. In farmer households though, no age criteria were used and the household was identified around the main agricultural holding unit of the enlarged household. This consists of the family members involved in the main production unit (land and livestock) in the enlarged household.

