### Test scores

Few studies have investigated the impact of school feeding on learning outcomes. Drèze *et al*. [32] reviewed the experimental evidence on the impact of school feeding on standardised test scores and found an average standardised effect size of 0.31 for math achievement tests, while no effect was found on reading tests. We adopt a 0.3 difference as the expected effect of the intervention on math test scores. Based on the Scrochet report, the recommended intra-cluster correlation coefficient for math and reading tests is 0.15. We also assume that only about half of the children interviewed will be able to take the test and we set the number of children tested per village at 25. Simulations of power as a function of minimum standardised detectable effect show that a standardised difference of 0.1 would be detected in 24% of cases, a difference of 0.2 would be detected in 68% of cases and a difference of 0.3 would be detected in 95% of cases. With power set at 80%, the minimum detectable difference is 0.23.

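### Covariate control cannot be said to overcome the selection that feeding creates among enrolled children; the learning analysis should rest on all household-sampled children as randomised

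*Protocol article*

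**What the plan says.** Methods of analysis notes that rural enrolment is around 30% and that "school feeding may bring to school children of very poor backgrounds with poor nutritional status and cognitive abilities to start with". It answers: "This problem can be overcome econometrically by controlling for such confounders during the data analysis". The same section lists the analysis sets ("The analysis will follow the intention to treat approach as protocol and as treated") and specifies a regression-adjusted difference-in-difference estimator.

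The article expects assignment to change enrolment. Main hypotheses and outcome indicators states: "The intervention will have a positive impact on enrolment, attendance and drop-out rates". The Enrolment part of Appendix 1 plans on a gain of five percentage points, and Impact on education treats extra schooling as one of the routes by which meals raise learning.

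On measurement, Main hypotheses and outcome indicators says: "All outcomes, including school attendance and test scores, will be obtained at the household level". Survey instruments puts the maths, language and digit span tests in the household questionnaire. Random assignment and manipulation of treatments describes the sample: "Households were randomly selected in the catchment areas of the selected schools for the survey interviews", and "A restricted household with children aged 5 to 15 was then randomly selected within each selected enlarged non-farmer household". Enrolment is not a selection criterion there.

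The Test scores part of Appendix 1 adds: "We also assume that only about half of the children interviewed will be able to take the test". It sets 25 tested children per village, against some 55 children per community earlier in the same appendix. It gives no reason for the half.

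**The concern.** The children drawn in by meals are not an ordinary confounding problem. Schools are randomised, so the arms are comparable until the comparison is conditioned on something that assignment changes. Being in school is such a thing. Among enrolled children, the treated arm contains entrants with no counterpart in the control arm's enrolled group. Regression removes the difference only if the measured covariates capture every joint driver of enrolment and score. Unmeasured ability and motivation are obvious gaps.

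Learning is among the primary outcomes in the Abstract. On the article's own description of the entrants, the distortion would run against the programme and grow as enrolment improves. A reader who takes the sentence at face value could treat an enrolled-only or as-treated result as safe after adjustment.

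**Working it through.** **1. The plan's own figure.** The Test scores part of Appendix 1 gives power of 24%, 68% and 95% at 0.1, 0.2 and 0.3 SD, and a minimum detectable difference of 0.23 SD. Inputs: K = 58 communes, J = 2 schools each, n = 25 children, ICC ρ = 0.15, alpha 0.05 (taken as two-sided). With a noncentral F on (1, K−1) df and λ = K·d² / [s² + 4(ρ + (1−ρ)/n)/J]:

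- ρ + (1−ρ)/n = 0.15 + 0.85/25 = 0.184, and 4 × 0.184/2 = 0.368.
- With s² = 0.01 (assumed effect variability), power is 23.0%, 68.3% and 95.5%, and the detectable difference is 0.230.
- With s² = 0, power is 23.5%, 69.4% and 95.9%, and the detectable difference is 0.227.

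The stated figures reproduce within 2 points and are not in dispute. They serve only as a scale.

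**2. Share of entrants among enrolled treated children.** Share = gain / (base + gain), with a gain of 0.05:

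- Base 30% (Methods of analysis): 0.05/0.350 = 14.3%.
- Base 35.1% (Table 6, attendance at ages 7 to 15): 0.05/0.401 = 12.5%.

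**3. Bias in an enrolled-only endline comparison.** Bias = −share × gap × (1 − r), where gap is how far entrants score below other enrolled children and r is the part of that gap removed by covariates. The article gives neither, so both are assumed.

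| Base | Gap (SD) | r = 0 | r = 0.5 | r = 1 |
|---|---|---|---|---|
| 35.1% | 0.3 | -0.037 | -0.019 | 0 |
| 35.1% | 1.0 | -0.125 | -0.062 | 0 |
| 30% | 0.3 | -0.043 | -0.021 | 0 |
| 30% | 1.0 | -0.143 | -0.071 | 0 |

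The bias vanishes only at r = 1, which is what the quoted claim requires.

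**4. Simulation.** Two independent standard normal drivers, one observed and one not, each enter both enrolment propensity and score with coefficient 0.5. Base enrolment is 35.1%, the true effect is 0.30 SD, and scores are taken at endline only.

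| Analysis | 5-point gain | 10-point gain |
|---|---|---|
| All sampled children, unadjusted | 0.30 | 0.30 |
| Enrolled only, unadjusted | 0.25 | 0.21 |
| Enrolled only, adjusted for observed driver | 0.27 | 0.25 |
| Enrolled only, adjusted for both drivers | 0.30 | 0.30 |

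The comparison of everyone sampled needs no adjustment. The enrolled-only comparison needs the unobserved driver.

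**5. Can the enrolment figures be carried over to testability?** Planned testing is 25/55 = 45% of children. If only enrolled children could be tested, the number per village would be 0.30 × 55 ≈ 17 to 0.351 × 55 ≈ 19, not 25. Testability is therefore not simply enrolment in this plan, and the shares in step 2 describe enrolled children, not test-takers.

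**The case against.** The strongest reply is that the design already contains the remedy. Scores are collected in households, households are sampled without regard to enrolment, intention to treat is listed first, and nothing in the article confines the learning analysis to enrolled pupils. This stands. A reader might infer that the trial's learning estimates will be biased; the article does not support that. Bias arises only if the comparison is restricted to enrolled children, to children whose testability depends on schooling, or to treatment as received.

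A reader might also infer that being able to take the test is itself a consequence of treatment. No reason is given for the half. In a sample starting at age 5 it could be age, which assignment cannot change.

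Third, difference-in-difference cancels a fixed level gap for children tested at both rounds, and Threats to validity describes the data as a panel. This stands too, and it means step 3 overstates the bias for that analysis. Differing score trends and changes in who is tested remain. A child who could not be tested at baseline has no baseline score to difference.

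Finally, the article refers to children's characteristics at the start, so it should not be read as planning to adjust for endline nutrition or cognition.

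None of this rescues the quoted sentence. If all sampled children are compared as randomised, the problem does not arise and the remedy is unnecessary; if enrolled children are compared, the remedy is inadequate. The second reading is not excluded: the section presents the matter as a difficulty for this analysis, lists as-treated analysis, and uses correlated test scores within a school as its clustering example.

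**Conclusion.** The point holds in conditional form. The article is wrong to say that controlling for confounders overcomes selection into school. Enrolled-only and as-treated learning results are open to selection on unmeasured factors, and testable-only results are too if testability depends on schooling. Intention to treat in all household-sampled children is free of selection on enrolment.

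The size is illustrative: about -0.04 to -0.14 SD before adjustment in an enrolled-only endline comparison, and about -0.02 to -0.07 SD if covariates remove half the gap. The planned effect is 0.3 SD and the stated detectable difference 0.23 SD. The range rests on the article's 5-point gain and its two base rates, and on an assumed gap of 0.3 to 1.0 SD for which the article gives no figure. It should not be read as a forecast of bias in the trial's intention-to-treat result.

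**What to change.** - Withdraw the statement that covariate control overcomes the selection.
- Make intention to treat in all household-sampled, age-eligible children, whatever their enrolment, the primary learning analysis.
- Set test eligibility on criteria that assignment cannot change, such as age. Scoring children who cannot attempt the test at the floor is an alternative, not a requirement.
- Adjust for baseline covariates only.
- Report enrolled-only, testable-only and as-treated learning results as secondary and subject to selection, for example with bounds.

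Trial oversight has the final analysis plan approved at the study's completion, so the learning population is best fixed before outcomes are known. The cost is mainly wording, an eligibility or scoring rule and slightly more analysis, using data already planned. The downside is some dilution of the effect, or skew in scores, from including children who are not in school.
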